## Exclusion Criteria

Exclusion criteria will be: (1) intellectual disability; (2) diagnosis of schizophrenia, schizoaffective disorder, delusional disorder, or other not specified psychosis-spectrum disorder; (3) having experienced depressive symptoms before pregnancy.

## Intervention

### Theoretical Background of the Experimental Intervention

Experimental intervention includes techniques derived from classic psychoeducation (63), motivational intervention (65, 66) and cognitive behavioral therapy (67). The intervention has been developed following the guidelines on the management of perinatal depression released by NICE (62), the American College of Obstetricians and Gynecologists (68) and the United States' Preventive Service Task Force (69). The adopted methodology included the following phases: (1) analysis of the scientific literature; (2) evaluation of available handbooks and manuals of other psychosocial interventions targeting perinatal depression; (3) focus groups with expert researchers, clinicians, users and carers, in order to identify the most relevant information to be included in the intervention; (4) development of an *ad-hoc* manual with a detailed description of each session of the intervention, booklets, and other written materials are provided to patients and relatives, whenever relevant; (5) evaluation of the feasibility of the “pilot” intervention in a small-size study.

### Features of the Experimental Intervention

The intervention consists in a uni-familiar psychoeducational intervention, scheduled every 7–10 days. It includes six modules on:
Individual and family assessment. This module is focused on the assessment of patients' personal and social functioning, and on the identification of personal goals. Moreover, the communication skills adopted by family members are evaluated as well as the characteristics of family functioning.Information on the clinical characteristics of the disorder and its treatment. In this module, information on the main clinical and epidemiological features of PD, including incidence, prevalence, long-term outcome, risk for the children, and negative impact on mother's mental health are presented. Moreover, available pharmacological and non-pharmacological treatment options are discussed, with a specific focus on the risk/benefit ratio for each approach and the importance to be compliant with the therapy. Moreover, during these sessions, the patient is invited to actively participate as the “expert,” describing her own personal experience. At the end of the session, an informative booklet will be provided to patients and their family members, summarizing the main aspects discussed during the session.Early warning signs. The third session is focused on the early warning signs of perinatal depression (e.g., changes in the number of sleeping hours; presence of irritability; anxiety; etc.) and on the importance to early detect such signs. In particular, patients are requested to identify, with the support of the mental health professional, their own warning signs and to report them on the “Schedule on early warning signs.” Strategies for preventing or managing crises are discussed and reported in the same schedule.Management of suicidal behaviors. This module is focused on suicidal risk and on the identification of warning suicidal signs. During this module, an *ad-hoc* schedule is provided to participants and family members in order to define a plan to be used in case of necessity.Communication skills sessions are focused on teaching strategies on how to express pleasant or unpleasant feelings, and on how to improve active listening. This module includes the use of role-plays and case vignettes, based on the personal experience of the patients and their family members.Problem solving skills. The last session is focused on teaching problem-solving techniques. Participants are invited to define a problem in their daily routine and to list all potential strategies to solve it. During the session, participants are guided by mental health professional to develop a plan for solving the problem and discuss possible advantages and disadvantages of each possible solution.

Each session lasts about 90 min. Moreover, two or more booster sessions are planned, if needed. Sessions are developed in order to stimulate discussion and interaction among participants. Site and frequency of sessions can be adapted to families' needs and mental health professionals' duties and workloads. The intervention will be carried out at the local mental health center and provided by trained mental health professionals, the time to complete all modules will be between 42 and 60 days. An *ad-hoc* manual has been developed by the research group in order to ensure treatment fidelity. Leaflets and other written materials will be given to patients and family members, when relevant (Table 1).

**Table 1 T1:** Characteristics of the interventions.

**PSYCHOEDUCATIONAL FAMILY INTERVENTION**
Uni-familiar psychoeducational intervention, scheduled every 7–10 days. It consists of six modules:
• Individual and family assessment
• Information on the clinical and epidemiological characteristics of the disorder
• Early warning signs
• Management of suicidal behaviors
• Communication skills
• Problem solving skills
Each session lasts about 90 min. Moreover, two or more booster sessions will be planned, if needed. Sessions are developed in order to stimulate discussion and interaction among participants. Leaflets and other written materials will be given to patients and family members when relevant.
**BEST TREATMENT OPTION (BTO)**
Provided according to the NICE guidelines
• Persistent subthreshold depressive symptoms/ mild to moderate depression: self-help and psychological counseling
• History of severe depression who initially presents with mild depression: pharmacological treatment
• Moderate or severe depression: high intensity psychological intervention, or pharmacological treatments, or an integration of both interventions.

### Control Intervention

Patients allocated in the control intervention will receive the best treatment option (BTO) according to the NICE guidelines (62). At each assessment point, the BTO will be documented through the use of the Pattern of Care Schedule (PCS), an *ad-hoc* schedule filled in by the researcher together with the treating psychiatrist. PCS aims to collect all the information related to the treatments received by the patient. Moreover, patients will continue to be in contact with the treating psychiatrist and whether necessary will receive psychological counseling, both individual, or familiar.

## Training of Mental Health Professionals

Three mental health professionals (at least one will be a psychiatrist) will receive an *ad-hoc* training course for the provision of the experimental intervention. Supervision meetings will be organized during the study period in order to ensure fidelity to the procedure.

## Ethical Issues

This study is being conducted in accordance with globally accepted standards of good clinical practice, in agreement with the Declaration of Helsinki and with national and local regulations. The study investigators ensure that all mental health professionals involved in the study are qualified and informed about the protocol, interventions, and trial-related duties. The study protocol has been submitted to the Ethical Review Board of the University of Campania “Luigi Vanvitelli.”

## Assessment Time and Instruments

Researchers participating to the study are blinded to patient allocation. All patients are assessed at the following time points: baseline (T0); 3 months post-randomization (T1); 6 months post-randomization (T2); 9 months post-randomization (T3); 12 months post-randomization (T4) (Table 2).

**Table 2 T2:** Assessment tools adopted in the study's protocol.

	**Screening phase**	**T0 (baseline)**	**T1 (month 3)**	**T2 (month 6)**	**T3 (month 9)**	**T4 (month 12)**
**ASSESSMENT INSTRUMENT**						
Edinburgh Postnatal Depression Scale (EPDS)	x					
Hamilton Depression Rating Scale (HAM-D)		x	x	x	x	x
Hamilton Anxiety Rating Scale (HAM-A)		x	x	x	x	x
Global Assessment of Functioning (GAF)		x	x	x	x	x
Clinical Global Impression (CGI)		x	x	x	x	x
Manchester Short Assessment of Quality of Life (MANSA)		x	x	x	x	x
Family Assessment Device (FAD)		x	x	x	x	x
Family Coping Questionnaire (FCQ)		x	x	x	x	x
Socio-demographic schedule		x	x	x	x	x
Pattern of Care Schedule (PCS)		x	x	x	x	x

The following questionnaires and schedules will be used during the study:
The Edinburgh Postnatal Depression Scale (EPDS) (64) is a simple and short 10-items self-report screening questionnaire initially developed for use in postnatal women to improve detection of postnatal depression. The EPDS allows health professionals to detect women who might need help and require a referral for a full diagnostic assessment. EPDS has satisfactory sensitivity and specificity values and it is also sensitive to changes in severity of depression over time. For the purpose of the present study, the cut-off threshold has been set at ≥ 10 (66). In validation studies, different cut-off points have been found due to clinical, social, cultural and economic diversities (70). The cut-off score for possible depression (i.e., a positive screening result) is ≥13 points but, as suggested by Hewitt et al. (71), a cut-off score ≥ 10 can be used in order to identify patients with both major or minor depression. Moreover, given the observed variability in the performance of the test, the screening procedure could produce both false positives and negatives (72). Therefore, it is essential that this screening tool is complemented by the clinical judgment (73).The Hamilton Depression Rating Scale (HAM-D) (74) is a 17-items questionnaire used to rate the severity of depressive symptoms such as low mood, insomnia, agitation, anxiety and weight loss. The interview and scoring take about 15 min. The score for each item ranges from 0 (not present) to 4 (extreme severity).The Hamilton Anxiety Rating Scale (HAM-A) (75) is a 14-items questionnaire developed to measure the severity of anxiety symptoms, both psychic anxiety (mental agitation and psychological distress) and somatic anxiety (physical complaints related to anxiety). The score for each item ranges from 0 (not present) to 4 (extreme severity).The Global Assessment of Functioning (GAF) (76) is a 100-point rating scale assessing social, occupational, and psychological functioning of adults, with higher scores indicating better level of functioning.The Clinical Global Impression (CGI) (77) scale measures illness severity (CGI-S), global change (CGI-C) and therapeutic response. The CGI-S is rated on a 7-point scale, from 1 (normal) to 7 (the most severely ill patients). The CGI-C scores range from 1 (very much improved) to 7 (very much worse). Treatment response ratings should take into account both the therapeutic efficacy and the treatment-related adverse events, and range from 0 (marked improvement and no side-effects) to 4 (unchanged or worse, and side-effects outweigh the therapeutic effects). Each component of the CGI is rated separately; the instrument does not provide a global score.The Manchester Short Assessment of Quality of Life (MANSA) (78) is a 17-item questionnaire assessing quality of life focusing on satisfaction in twelve aspects of life. For twelve items, the satisfaction is rated on 7-point rating scales, ranging from 1 (“could not be worse”) to 7 (“could not be better”). For five items, the responses are binary (“yes” or “no”). The total MANSA score is the mean of the Likert-item scores.The Family Assessment Device (FAD) (79), based on the McMaster Model of Family Functioning, consists of 7 subscales on family involvement in patient's care (affective involvement, affective responsiveness, behavioral control, communication, problem solving, and roles and general family functioning). Scores range from 1 (“healthy functioning”) to 4 (“unhealthy functioning”).The Family Coping Questionnaire (FCQ) (80) is a self-administered 34-items questionnaire, which has shown a good reliability and external validity. Each item is rated on a 4-level scale, from 1 (“never”) to 4 (“always”). The items are grouped into the following 11 subscales: information on patient's illness; positive communication toward the patient; relatives' maintenance of social interests; patient's involvement in social activities; talking with friends about the patient's condition; coercion; avoidance; resignation; use of alcohol and drugs; collusion; search for spiritual help. The FCQ is widely used for the assessment of coping strategies among relatives of people with severe mental disorders (81, 82).The Pattern of Care Schedule (PCS) (80), a 40-item questionnaire on pharmacological and non-pharmacological treatments as well as on health care access made by the patient. It is compiled by the researcher in collaboration with the patient. If information is inadequate, or if the researcher is not sure about patients' reliability, other sources (e.g., treating physician, relatives, etc.) can be consulted. During the study period, the treating clinician will continue to provide the usual treatment to patient, and–if necessary–to change or adjust the pharmacological regimen. This schedule is used in order to record pharmacological treatments and doses, psychotherapeutic and psychosocial interventions (type of intervention, number of sessions) provided to patients in order to document the BTO.

## Baseline Assessments

At baseline the following information will be collected: (1) sociodemographic data (age, nationality, educational level, marital status, employment status, number of family members, duration of the illness, time in charge at the mental health center (months), number of (voluntary and involuntary) hospitalizations, suicide attempts (numbers); (2) clinical features related to pregnancy (gestational period, previous pregnancies, *in vitro* fertilization, clinical conditions of the fetus, and the pregnant); (3) social context, such as relationship with the partner, family conflicts, socio-economic stressors, history of any psychiatric disorder (Table 3).

**Table 3 T3:** Baseline assessments.

**Sociodemographic data**	**Clinical features related to pregnancy**	**Social context**
• Age	• Gestational period	• Relationship with the partner
• Nationality	• Previous pregnancies	• Family conflicts
• Educational level	• *In vitro* fertilization	• Socio-economic stressors
• Marital status	• Clinical conditions of the fetus and the pregnant	• History of any mental disorder
• Employment status		
• Number of family members		
• Duration of the illness		
• Time in charge at the mental health center		
• Number of hospitalizations		
• Suicide attempts		

## Statistical analyses

### Power Analysis

In order to assess the efficacy of the experimental intervention, a power analysis was performed. As reported by Sockol et al. (83), available psychosocial interventions for perinatal depression have been found to have an overall effect size of 0.65. Therefore, the sample size has been defined selecting 0.65 as desired level of effect size, an α error set at 0.05 and power set at 0.95. Therefore, the total sample will consist of 126 patients, allocated with a 1:1 ratio to the experimental or to the control group (Figure 1).

### Data Analysis

Differences in socio-demographic and clinical characteristics, such as severity of depressive and anxiety symptoms, quality of life, trimester of pregnancy, and personal functioning between the two groups will be evaluated using Chi-square or *T*-test for independent samples, as appropriate. Differences in coping strategies and in family accommodation reported by relatives will be evaluated with the same tests.

In order to assess the efficacy of the experimental intervention, a linear multivariable regression model will be implemented, using as main outcome the score at HAM-D at 3 months post-randomization. Moreover, several confounding variables (such as age, marital status, familiarity for mental disorders, peer support, previous pregnancy, etc.) will be entered in the model. Furthermore, predictors of response at the end of the intervention will be identified.

“Response” is generally defined as a 50% decrease in scores on Hamilton Depression Rating Scale (HAMD) (74). In this protocol, we will consider the score at the 3-month HAM-D compared with the baseline score. Therefore, the continuous variable “3-month HAM-D score” will be transformed in a binary variable (1 = response; 0 = absence of response), and it will be entered in a logistic regression multivariate model in order to identify possible predictors of positive response to the experimental intervention.

In order to evaluate differences in relatives' coping strategies according to patients' clinical features and type of relationship with the patient, a two-level model with fixed independent variables and random intercept, using a maximum likelihood estimation, will be performed. The mean score at the subscales of the FCQ will be entered in the model, adding covariates step by step in order to identify the model with indexes of best fit. The final model will be selected according to the−2 loglikelihood value, and the model with the lowest value will be choose. Estimate, standard error, 95% confidence interval, and *P*-values will be calculated.

The level of significance will be set at *p* < 0.05. All analyses will be performed using the Statistical Package for Social Science software (SPSS), version 18.0 (SPSS).

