## Inclusion Criteria

Starting from January 2019, patients attending the outpatient unit of Gynecology and Obstetrics of the University of Campania “Luigi Vanvitelli” will be invited to participate to the study. The eligibility criteria will be: (1) gestation age > 3 months or within 3 days of childbirth; (2) age ≥ 18 years; (3) absence of any disabling physical condition; (4) living with a relative for at least 9 months in the last year and continuously in the last 3 months.

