One of the main strengths of our study is represented by the adaption of a well-known family psychoeducational model to the treatment of perinatal depression. In particular, the Falloon psychoeducational intervention was developed for the community management of schizophrenia (63, 90) and has been subsequently adapted to the management of major depression (59, 91) and bipolar disorder (57, 92–94). Perinatal depression may represent an ideal target for this kind of interventions, since it is highly dependent from stressful life events and from family context. Moreover, peripartum is a period of women's life in which pharmacological treatments should be used very cautiously and only in a limited situations. Another strength of our study is the rigorous methodology adopted, which will allow us to understand the impact of the experimental intervention on patient's outcome through a randomized controlled approach. Moreover, the main outcome is the reduction of depressive symptoms at 3-months after randomization. This is an ambitious outcome, since many confounding variables can impact on it. In particular, in some cases the childbirth represents itself an event associated with a reduction of depressive symptoms (95), thus biasing the effectiveness of the experimental intervention. Moreover, other contextual factors (such as support by family members, changes in the daily routine following the childbirth, or starting a pharmacological treatment) can have an impact on the long-term outcome. We aim to control for such variables using a statistical procedure, in order to accommodate for the impact of all these confounding variables.

Furthermore, the postnatal psychoeducation programme is suitable for clinical use as it is relatively brief and can be delivered by postnatal unit nurses and midwives after a short period of training.

Another strength of this study is the use of the EPDS as screening measure, which will allow comparisons with data from other international studies.

In order to detect patients affected by both major and minor depression, the cut-off at EPDS of ≥10 has been selected (71) and it will have to be complemented by the clinical judgment (96).

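### The 3-month HAM-D regression does not pre-specify baseline HAM-D or pregnancy/postpartum stage at entry as covariates, although both are collected at baseline

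*Protocol article*

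**What the plan says.** Under Data Analysis, efficacy is to be assessed thus: "a linear multivariable regression model will be implemented, using as main outcome the score at HAM-D at 3 months post-randomization". The covariates are then described: "several confounding variables (such as age, marital status, familiarity for mental disorders, peer support, previous pregnancy, etc.) will be entered in the model". Five are named, and the list is open at both ends (*such as*, *etc.*).

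Baseline HAM-D is not among the five. It is collected: in Table 2 the row beginning "Hamilton Depression Rating Scale (HAM-D" is marked at T0 and at every follow-up. Stage of pregnancy at entry is not named either, although Baseline Assessments and Table 3 record the gestational period. Previous pregnancy, which is named, is obstetric history and does not say whether a woman is pregnant or has just delivered.

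Baseline severity and trimester do appear in Data Analysis, but only among the characteristics compared between arms by chi-square or t-test. Baseline HAM-D also enters the definition of response, which feeds a separate logistic model.

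The eligibility window is "gestation age > 3 months or within 3 days of childbirth". Patients' Recruitment Procedure describes 1:1 randomisation and mentions no stratification. The Discussion notes that "in some cases the childbirth represents itself an event associated with a reduction of depressive symptoms" and adds that such influences will be controlled by a statistical procedure that it does not name.

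**The concern.** The model's outcome is a raw follow-up score. The baseline value of the same scale is usually one of the better predictors of such a score, and here it costs nothing extra to collect. If the final model omits it, the interval is wider than it need be, and a chance difference in starting severity is carried, in part, into the treatment effect.

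Stage at entry matters for a reason that the article itself gives. At the 3-month visit, a woman who entered early in the window may still be pregnant, one who entered late in pregnancy will have delivered in between, and one who entered just after birth will be about three months postpartum. If childbirth can change symptoms, stage at entry is prognostic for the 3-month score. The between-arm tests would show an imbalance in either variable but would not correct the estimate for it.

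**Working it through.** **Inputs from the article (Power Analysis).** "the sample size has been defined selecting 0.65 as desired level of effect size"; "an α error set at 0.05 and power set at 0.95"; "the total sample will consist of 126 patients, allocated with a 1:1 ratio to the experimental or to the control group". So d = 0.65 (SD = 1), α = 0.05, power 0.95, 63 per arm.

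**Input not in the article.** The correlation r between baseline and 3-month HAM-D. It is assumed here and shown over 0.3 to 0.6.

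**Step 1: reproduce the sample size.** A two-sided two-sample t-test (noncentral t) with d = 0.65 first reaches power 0.95 at 63 per arm, total 126, with power 0.9515. The two-sided normal approximation gives 62 per arm (124). A one-sided test gives 104 and does not match. The stated 126 is therefore the unadjusted two-sided figure and relies on no covariate.

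**Step 2: effect of adjusting for baseline HAM-D.** The variance of the treatment effect is multiplied by 1 − r², and the interval width by √(1 − r²). Power uses a noncentral t with 126 − 3 = 123 degrees of freedom and noncentrality d/√(1 − r²) × √(63/2).

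| r (assumed) | Interval width factor | Power, d = 0.65 | Power, d = 0.50 | Total N for 0.95 at d = 0.65 |
|---|---|---|---|---|
| 0 (unadjusted) | 1.000 | 0.952 | 0.795 | 126 |
| 0.3 | 0.954 | 0.967 | 0.831 | 114 |
| 0.5 | 0.866 | 0.987 | 0.895 | 96 |
| 0.6 | 0.800 | 0.995 | 0.936 | 82 |

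The d = 0.50 column is an illustration of a smaller true effect; that value is not in the article. The interval narrows by 1 − 0.954 ≈ 5% at r = 0.3 and by 1 − 0.800 = 20% at r = 0.6.

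**Step 3: chance imbalance in baseline HAM-D.** Without stratification, the standard error of the baseline difference is √(2/63) = 0.178 SD. The chance of a difference above 0.2 SD in either direction is 2 × [1 − Φ(0.2/0.178)] ≈ 26%; above 0.3 SD it is about 9%. An unadjusted estimate moves by r times the imbalance (equal SDs at the two visits assumed). For 0.2 SD that is 0.3 × 0.2 = 0.06 SD to 0.6 × 0.2 = 0.12 SD.

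**Step 4: chance imbalance in stage at entry.** The share p entering postpartum is not given. The standard deviation of the difference between arms is √(2p(1 − p)/63): 0.053, 0.082 and 0.089 for p = 10%, 30% and 50%. The chance of a difference above 10 percentage points is then about 6%, 22% and 26%.

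**Step 5: cost if the covariates turn out uninformative.** The variance is inflated by about 123/122 = 1.008 for one covariate, 123/121 = 1.017 for two and 123/120 = 1.025 for three. Power at d = 0.65 stays at about 0.951.

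**The case against.** The strongest reply is that the list is illustrative. Nothing in it rules out baseline HAM-D or stage at entry, and an article may leave the final covariate set to a fuller document. A reader might infer that the plan excludes these variables; the text does not support that. What stands is that the article chose to state the model and give examples, left out the most natural covariate, and left the list open.

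The Discussion's promise of statistical control might seem to fill the gap. It names no baseline term. The influences it lists (childbirth, family support, altered routine, starting medication) arise largely after randomisation. Family support could itself be changed by a family intervention, so adjusting for it could remove part of the effect.

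A reader might also infer that the effect estimate is biased or the trial underpowered. Neither follows. Randomisation keeps the unadjusted estimate unbiased on average, and power at the planned effect is already 0.95. Nor does an imbalance pass in full into the estimate; it enters in proportion to the slope of outcome on baseline.

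Finally, the gains in the table are measured against an unadjusted test, whereas the plan already adjusts for other variables. If those share variance with baseline HAM-D, the gain is smaller. No figure in the article shows the named covariates to be weak, and several are not demographic. It also gives no HAM-D standard deviation, so how widely baseline severity will vary is unknown.

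**Conclusion.** The point holds as a matter of specification. The stated model omits from its named covariates a baseline value that is already collected, and a stage variable that the article's own reasoning makes prognostic. The expected benefit of naming baseline HAM-D is an interval about 5 to 20% narrower and protection against an imbalance above 0.2 SD that would arise in about one trial in four. These sizes rest on an assumed correlation of 0.3 to 0.6, equal SDs at the two visits, and an unadjusted comparator. The loss occurs only if the final model leaves the variables out. At d = 0.65 the power gain is small; the benefit matters more for precision and if the true effect is smaller than planned. It is a worthwhile improvement, not an error that invalidates the analysis.

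The Primary Outcome section defines the primary outcome as a reduction of at least 50% in HAM-D, while Data Analysis models the continuous score. That conflict is separate and is not settled here.

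**What to change.** In Data Analysis, before unblinding:

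- Name T0 HAM-D, and pregnant/postpartum status with gestational stage at T0, as fixed covariates in the 3-month HAM-D model.
- Delete the *etc.* and give the full covariate list.
- Restrict it to variables measured at baseline. Peer support, for example, does not appear under that name in Table 3, so either identify its baseline source or drop it.
- For continuous secondary outcomes rated by the patient or clinician, adjust for the corresponding baseline value. The relatives' FCQ has its own two-level model in the article and should be handled within that model.

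No new data are needed. The statistical cost is one or two degrees of freedom, about 1 to 2% of variance if the covariates prove uninformative, or about 2.5% if stage is coded as a third term.

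### The search for predictors of response cuts the 3-month HAM-D score to yes/no before modelling, which under plausible assumptions costs roughly 10 to 30 points of power for moderate effects

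*Protocol article*

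**What the plan says.** The Data Analysis section first sets out a linear multivariable regression of the 3-month HAM-D score to assess efficacy. It then turns to predictors. Response "is generally defined as a 50% decrease in scores on Hamilton Depression Rating Scale (HAMD", taken at 3 months against baseline. The 3-month score "will be transformed in a binary variable (1 = response; 0 = absence of response), and it will be entered in a logistic regression multivariate model", and the stated purpose is to "identify possible predictors of positive response to the experimental intervention". No other method for finding predictors is described. The same section adds: "The level of significance will be set at *p* < 0.05".

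Table 2 shows HAM-D collected at baseline and at month 3, so both scores are planned for every woman.

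The Power Analysis section sizes the trial by "selecting 0.65 as desired level of effect size", with "an α error set at 0.05 and power set at 0.95", and concludes that "the total sample will consist of 126 patients, allocated with a 1:1 ratio". It states no power for the predictor analysis.

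Under Anticipated Results, the Primary Outcome section names a HAM-D reduction of at least 50% at 3 months.

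**The concern.** Once the score is cut, a woman who improves by 49% counts the same as one who gets worse, and a woman who improves by 51% counts the same as one in full remission. The model can no longer use those differences. A baseline characteristic that shifts the 3-month score is therefore harder to detect from the binary variable than from the score itself.

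This matters because the predictor search is the analysis meant to say which women do well with the intervention, and the trial was not sized for it. Real predictors become more likely to be missed, although the fuller measurement is already available at no extra cost.

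**Working it through.** **1. The plan's own figure.** Two-sided t-test, effect size 0.65, alpha 0.05, 63 per arm: power is 0.9515, against 0.9485 with 62 per arm. So 63 × 2 = 126 reproduces. A one-sided test would need only 104. The trial is thus sized for one two-group contrast on a continuous scale.

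**2. Information kept by the cut.** For a normally distributed outcome cut so that a proportion p respond, the share of information kept for a modest effect is φ(z_p)² / [p(1 − p)].

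- p = 0.5: 0.3989² / 0.25 = 0.637, so 126 women act like 126 × 0.637 ≈ 80.
- p = 0.2: 0.2800² / 0.16 = 0.490, so 126 women act like 126 × 0.490 ≈ 62.

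**3. What that means for power.** Take a predictor that splits the 126 women in half and shifts the 3-month score by 0.5 SD (assumed).

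- Continuous: 0.5 × √(63/2) = 2.806; power = Φ(2.806 − 1.96) = 0.80.
- Cut at p = 0.5: 2.806 × √0.637 = 2.24; power = Φ(0.28) ≈ 0.61.
- Cut at p = 0.2: 2.806 × √0.490 = 1.96; power = Φ(0.00) ≈ 0.50.

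Comparing the two proportions directly gives 0.60 and 0.48. Other predictor sizes, by the same direct comparison for response rates of 20 to 50%:

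| Predictor effect (SD) | Power, continuous | Power, binary | Loss (points) |
|---|---|---|---|
| 0.2 | 0.20 | 0.12–0.14 | 6–8 |
| 0.3 | 0.39 | 0.21–0.27 | 13–18 |
| 0.5 | 0.80 | 0.48–0.60 | 20–32 |
| 0.65 | 0.95 | 0.69–0.82 | 13–26 |
| 0.8 | 0.99 | 0.85–0.95 | 5–15 |

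**4. Simulation with the actual response definition.** The formulas above treat response as a cut of the 3-month score. In the plan it is a cut relative to each woman's baseline, so this was simulated.

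- From the protocol: 126 women 1:1, arm effect 0.65 SD, response at a 50% fall, alpha 0.05.
- Assumed: baseline mean 20, SD 4; 3-month SD 6; correlation 0.4; control 3-month mean 11, 13 or 15.

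Implied response rates: 3-month score minus half of baseline has variance 36 + 4 − 2 × 0.5 × 0.4 × 6 × 4 = 30.4, so SD 5.51. The arm effect is 0.65 × 6 = 3.9 points.

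- Control mean 11: Φ(−1/5.51) = 0.43 in control and Φ(2.9/5.51) = 0.70 in the experimental arm; overall about 56%.
- Control mean 15: Φ(−5/5.51) = 0.18 and Φ(−1.1/5.51) = 0.42; overall about 30%.

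The linear and logistic models used the same data and the same terms, both adjusted for baseline, and for arm where both arms were used:

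| Term tested | Linear | Logistic |
|---|---|---|
| Continuous predictor by arm, slope difference 0.65 SD | 93–97% | 71–79% |
| Continuous predictor by arm, slope difference 0.5 SD | 77–82% | 51–62% |
| Binary predictor by arm, difference 1.0 SD | 79–84% | 54–67% |
| Binary predictor by arm, difference 0.65 SD | 46% | 27–35% |
| Experimental arm only (63), binary predictor, 0.65 SD | 76–79% | 57–61% |

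Repeat runs moved individual losses by several points, so these settings are best summarised as roughly 10 to 30 points.

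**5. Where the loss shrinks.** Interactions of 0.2 to 0.3 SD lose about 1 to 11 points, because power is low either way. A binary main effect of 0.8 SD loses about 2 to 5 points, and a continuous main effect of 0.5 SD or more loses about none, because power is near its ceiling either way.

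**The case against.** The strongest reply is that the binary variable is not arbitrary. The Primary Outcome section names a 50% reduction at 3 months, so a logistic model of response asks directly which women reach an outcome that the protocol cares about, and odds of response are easy for clinicians to read. This stands. It is a reason to keep the logistic model, but not to make it the only tool for finding predictors.

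Second, the efficacy regression already uses the continuous score with several covariates, and its coefficients say something about prognosis. That is true in part, but those covariates are entered as confounders, and the method set out for identifying predictors is the logistic one.

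Third, the two models do not test quite the same hypothesis: points on an absolute scale against odds of a percentage fall. The simulation also generates data on a normal scale, which suits the linear model. Both points are fair. Some of the gap reflects scale and distribution as well as the cut, which is a further reason to treat the figure as approximate.

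Fourth, this is a secondary analysis of possible predictors, with no power claimed for it. That limits the weight of the point. It does not justify discarding information when keeping it costs one sentence.

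**Conclusion.** The point holds as an inexpensive improvement to a secondary analysis. The plan fixes a cut that throws away information already collected. Under the assumptions listed (baseline mean 20, SD 4; 3-month SD 6; correlation 0.4; response about 30 to 56%), the cost is roughly 10 to 30 points of power for moderate predictor effects, and less, sometimes near zero, at either extreme.

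A reader might infer more than this, and the documents do not support it:

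- **That the loss is a fixed property of the plan.** It is not. The protocol gives neither a response rate nor a predictor effect, and the loss varies with both.
- **That the efficacy result is weakened.** The efficacy model described in Data Analysis keeps the continuous score and is untouched by this point.
- **That the logistic model has too few events for its covariates.** The covariate list in the article belongs to the linear efficacy model. The logistic model's terms are not listed, and a condensed article may leave them to a fuller document.
- **That no guideline calls for the cut.** The cited sources are not at hand, so this cannot be checked.

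The wording also leaves open whether the model uses all 126 women or only the 63 in the experimental arm. With 63, power starts lower for both models.

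**What to change.** In Data Analysis, replace the sentence that sends the binary variable to a logistic model. The main predictor analysis becomes a linear model of the 3-month HAM-D score with baseline HAM-D as a covariate and the same candidate predictor and treatment terms that the logistic model would have held. Keep the logistic model of 50% response, together with response rates by arm and by predictor level, as a supporting analysis that ties back to the Primary Outcome section.

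This needs no new data, visits or patients. The one small cost is that the main predictor effects are read in HAM-D points; the supporting analysis still supplies odds ratios and response rates.
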